### Sample size calculation

This trial is an open-label randomized clinical trial, so patients will randomly be assigned to olmesartan medoxomil or conventional antihypertensive medication groups (1:1 ratio). The purpose of this study is to verify that olmesartan medoxomil is effective in the treatment of coronary atherosclerosis progression and EAT volume reduction in patients with coronary atherosclerosis detected by CCTA. We also want to elucidate the relationship between coronary atherosclerosis and EAT. The mechanism by which olmesartan medoxomil inhibits coronary atherosclerosis progression will be studied by detecting the serum levels of blood lipids, glucose, circulating surrogate markers of atherosclerosis inflammation including high-sensitivity C-reactive protein, IL-6, MCP-1, TNF-α, and MMP-9, circulating surrogate markers of endothelial function, including NO and ET-1, and circulating surrogate markers of adipose tissue inflammation and metabolism, including adiponectin and leptin.

Studies on coronary atherosclerosis progression rate have had differing results. The combined results of multiple studies indicate that the conventional mean coronary atherosclerosis progression rate is about 30 % [33–35]. We hypothesize that additional olmesartan medoxomil use will reduce the coronary atherosclerosis progression rate to 13 % [36–40]. Using double-side inspection, α = 0.05, β = 0.2, we calculate a total sample size of 176 cases; considering the expected loss to follow-up to be 10 %, the number of cases to be included should be at least 176 × (1 + 10 %) = 194. Therefore, we aim for 97 cases of each group.

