### Follow-up

Clinical follow-up will take place at 1 month (±1 week), 3 months (±2 weeks), 6 months (±2 weeks), 9 months (±30 days), and 1 year (±30 days) by clinical visit or phone interview.

At baseline and 6-month (±2 weeks) and 1 year (±30 days) follow-ups, all patients will provide venous blood for detection of blood lipids, glucose, high-sensitivity C-reactive protein, IL-6, MCP-1, TNF-α, NO, ET-1, MMP-9, adiponectin, and leptin.

At 1 year (±30 days) follow-up, all patients will undergo CCTA (with QAngio CT post-processing software).We anticipated a patient drop-out rate of 10 %.

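### The 10 % drop-out allowance multiplies by 1.10 instead of dividing by 0.90, so 194 enrolled leave about 174–175 evaluable against the required 176 (minor)

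*Protocol article*

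**What the plan says.** The section on sample size calculation in the protocol article sets out its inputs in full. For the control group it takes "the conventional mean coronary atherosclerosis progression rate is about 30" %. For the active group it supposes that "additional olmesartan medoxomil use will reduce the coronary atherosclerosis progression rate to 13" %. The error rates are given as "Using double-side inspection, α = 0.05, β = 0.2", and allocation is 1:1. From these, "we calculate a total sample size of 176 cases".

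The drop-out step follows at once. With 10 % expected loss to follow-up, "the number of cases to be included should be at least 176" times (1 + 10 %), and the product is printed as 194. The quoted words stop just before the multiplier, so 176 is the number to be inflated and not the enrolment target. The section ends: "Therefore, we aim for 97 cases of each group".

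The follow-up section gives the same 10 %, and describes it as a rate among patients: "We anticipated a patient drop-out rate of" 10 %.

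**The concern.** A drop-out rate applies to the patients who are enrolled. To have 176 left after losing 10 % of N, N must satisfy N × 0.90 = 176. Adding 10 % of 176 answers a different question and always gives too small a number. The article presents 194 as the minimum that secures 176 evaluable patients, and under its own loss rate it does not do so.

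What is at stake is whether the sample size statement is internally correct and whether the 80 % power survives the expected loss. The multiplication is written out in the text, so this is a wrong statement and not a detail that a condensed article leaves to a fuller document.

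**Working it through.** **Inputs, all from the sample size section:** progression rates p1 = 0.30 and p2 = 0.13, difference 0.17; two-sided α = 0.05 (z = 1.960); β = 0.2 (z = 0.8416); 1:1 allocation; loss to follow-up 10 %, repeated in the follow-up section.

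**1. Reproduce the 176.** Normal approximation with unpooled variance:

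n per arm = (1.960 + 0.8416)² × (0.30 × 0.70 + 0.13 × 0.87) / 0.17²
= 7.849 × 0.3231 / 0.0289 = 87.75, rounded up to 88.

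Two arms give 176, which matches the article exactly.

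**2. Reproduce the 194.** 176 × 1.10 = 193.6, rounded up to 194, or 97 per arm. This also matches.

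**3. Apply the stated loss to the enrolled number.** 194 × 0.90 = 174.6, so 174 or 175 evaluable (87.3 per arm). That is 1 to 2 below 176.

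**4. Loss that 194 can absorb.** (194 − 176) / 194 = 18 / 194 = 9.3 %. The expected loss is 19.4 patients.

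**5. Correct inflation.** 176 / (1 − 0.10) = 195.6, rounded up to 196, or 98 per arm. Check: 196 × 0.90 = 176.4.

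**6. Effect on power at 30 % versus 13 %.** For the unpooled formula, power = Φ(0.17 / √(0.3231 / n) − 1.960). The exact column sums binomial probabilities over all outcomes that the uncorrected Pearson chi-square test rejects.

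| Evaluable per arm | Unpooled formula | Exact Pearson chi-square |
|---|---|---|
| 88 (required) | 80.1 % | 79.8 % |
| 87.3 (= 174.6 / 2) | 79.8 % | – |
| 87 | 79.7 % | 79.3 % |

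The inflation error therefore costs between about 0.3 points (unpooled, 88 to 87.3) and 0.6 points (exact, 88 to 87).

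**The case against.** The best reply is that this does not matter in practice. The correct total differs from the printed one by two patients. The 10 % loss is only an expectation, and a realised loss of 9.3 % or less would still leave 176. The 30 % control rate is itself approximate, and the section says that earlier studies had differing results; that uncertainty outweighs two patients. All of this stands, and it is why the point is minor. It does not make the printed step correct: the number is offered as a minimum under a 10 % loss, and under that loss it falls short.

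A reader might also infer something stronger: that the trial is clearly underpowered, or that 176 is itself too small for a chi-square test. The documents do not support either reading.

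- A pooled-variance formula gives 78.4 % power at 87 per arm, and a continuity-corrected chi-square test gives 73.4 %. At the full 88 per arm the same two methods already give 78.9 % and 74.0 %. Almost all of the gap to 80 % comes from changing the method, and the drop-out step adds only about 0.5 to 0.6 points.
- The unpooled formula is a standard method and reproduces 176 exactly. The Pearson test at 88 per arm has 79.8 % power by exact enumeration, in effect the 80 % claimed.
- The statistical analysis section names chi-square tests and mentions no continuity correction. Which variant is used is detail that an article may leave to the full plan, so its absence is no finding.

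**Conclusion.** The point holds as a minor arithmetic error. As printed, the allowance for loss does not deliver the number that the plan says it needs: enrolment is short by two patients (one per arm), and at the stated loss 174 to 175 remain evaluable. Power moves from about 80 % to just under it. No conclusion of the trial depends on this.

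The result assumes that the 10 % is a proportion of enrolled patients, as the follow-up section's wording indicates, and that the losses fall about equally on the two arms. The power figures also rest on the article's own rates of 30 % and 13 %.

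**What to change.** Either of two changes makes the statement true.

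- **Keep 194 and restate what it delivers:** 194 enrolled, about 174 evaluable after 10 % loss, power just under 80 % (about 79.7 % by the unpooled formula, 79.3 % by exact Pearson enumeration). This costs one sentence and no patients.
- **Correct the formula:** 176 / (1 − 0.10) = 196, or 98 per arm. This costs two more patients. The trial status section reports recruitment as ongoing, so it was feasible when the article was written. The total of 194 in the abstract and the 97 per group would change with it.

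The figure of 176 needs no change.

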### Statistical analysis

Continuous variables will be described using means and standard deviations or median and range in case of asymmetric distribution of data. Categorical variables will be presented using frequency distribution. Univariate analyses will be conducted using chi-square and *t* tests for independent samples. A multiple logistic regression analysis will be performed to correlate coronary atherosclerosis progression with clinical variables and EAT volume, including treatment groups. Statistical significance will be considered for *P* < 0.05. A statistical package (SPSS 16.0) will be used for analysis. The individual will be considered the unit of analysis.

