### Randomization

Information regarding the study will be provided to the patient at the Department of Cardiology. Once informed consent is obtained, the patient will be randomized at the Department of Cardiology. Subjects will be randomized to either olmesartan medoxomil or conventional antihypertensive medication groups (1:1 ratio). Participants will be randomized before the first treatment using a blocked randomization procedure (computerized random numbers) and will incorporate minimization to ensure matching for age, sex, body mass index, and hypertension grade.

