### Study outcomes

The primary outcome measures are coronary atherosclerosis progression and EAT volume changes, as detected by CCTA at 12 months.

The secondary outcome measures includeThe relationship between coronary atherosclerosis and EAT;Serum levels of blood lipids, glucose, circulating surrogate markers of atherosclerotic inflammation including high-sensitivity C-reactive protein, IL-6, MCP-1, TNF-α, and MMP-9, individual circulating surrogate markers of endothelial function including NO and ET-1, and individual circulating surrogate markers of adipose tissue inflammation and metabolism including adiponectin and leptin at baseline and after 6 and 12 months.

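### The primary EAT comparison has no covariate-adjusted model and no planned analysis names the four minimisation factors: precision is given up and the test may be conservative, but false positives are not inflated

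*Protocol article*

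**What the plan says.** All references are to the protocol article.

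- **Randomization.** Patients are allocated 1:1 by a blocked procedure that "will incorporate minimization to ensure matching for age, sex, body mass index, and hypertension grade".
- **Study outcomes.** There are two primary outcomes: coronary atherosclerosis progression, which is binary by its definition in the CCTA section, and "EAT volume changes, as detected by CCTA at 12 months".
- **Statistical analysis.** The two-group methods are given in one sentence: "Univariate analyses will be conducted using chi-square and" t tests for independent samples. The next sentence plans a multiple logistic regression relating progression to clinical variables and EAT volume, with treatment group among the terms. No model is given for EAT volume as an outcome.
- **Inclusion criteria and EAT quantification.** Eligibility requires a CCTA, and EAT is measured on the same images as the CCTA. A baseline EAT volume should therefore exist for every randomised patient.

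**The concern.** Minimisation forces the arms to be alike on four factors. If those factors predict the outcome, the true sampling variance of the treatment difference is smaller than a two-sample test assumes. Its standard error is then too large and its actual type I error falls below the nominal 5 %. Including the factors in the model restores the calibration and recovers the power.

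Baseline EAT raises a separate issue. Subtracting baseline from follow-up is a fixed adjustment with slope 1. ANCOVA estimates the slope and is at least as precise in large samples.

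The stake is efficiency on a primary outcome. The sample size was set on progression alone, so the article documents no power margin for EAT. The covariates needed are all known before treatment starts.

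**Working it through.** **1. The plan's own figure.** The inputs come from Sample size calculation: "Using double-side inspection, α = 0.05, β = 0.2, we calculate a total sample size of 176 cases"; a control rate given as "conventional mean coronary atherosclerosis progression rate is about 30" per cent; and a treatment effect expected to "reduce the coronary atherosclerosis progression rate to 13" per cent. With the unpooled two-proportion formula:

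n per arm = (1.960 + 0.842)² × (0.30×0.70 + 0.13×0.87) / 0.17² = 7.849 × 0.3231 / 0.0289 = 87.7, rounded up to 88, or 176 in total.

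This reproduces the stated 176. The section gives no SD, effect or power for EAT. I use 88 per arm below. The target of 97 per group less 10 % is 97 × 0.9 = 87.3, and 87 per arm gives the same results.

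**2. EAT: t test on change against ANCOVA on baseline.** Let r be the baseline to 12-month correlation, with equal variance σ² at both times. The document gives no r, so the values are assumed.

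- Variance of change: 2σ²(1 − r)
- ANCOVA residual variance: σ²(1 − r²)
- Ratio of ANCOVA to change: (1 + r)/2
- ANCOVA power where the change-score test has 80 %: Φ(2.802/√((1 + r)/2) − 1.960)

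| r | Variance ratio | ANCOVA power |
|---|---|---|
| 0.5 | 0.75 | 90 % |
| 0.7 | 0.85 | 86 % |
| 0.8 | 0.90 | 84 % |
| 0.9 | 0.95 | 82 % |

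**3. EAT: omitting the minimisation factors.** Let R² be the share of variance in the analysed outcome that the four factors explain. It is assumed, since the document gives none. Under perfect balance, the type I error of the unadjusted test is 2[1 − Φ(1.960/√(1 − R²))]. A simulation of minimisation (176 patients, four factors, an assumed 80 % biased coin) checks the formula.

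| R² | Type I error, formula | Type I error, simulated | Power, unadjusted vs adjusted |
|---|---|---|---|
| 0 | 5.0 % | 5.0 % | 80 vs 80 % (formula) |
| 0.1 | 3.9 % | 3.8 % | 80 vs 83 % (simulated) |
| 0.2 | 2.8 % | 3.3 % | 82 vs 88 % (simulated) |
| 0.3 | 1.9 % | 1.9 % | 84 vs 91 % (simulated) |

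The factor-adjusted test stayed at 4.6 to 5.3 %. The gains in steps 2 and 3 should not be added, because baseline EAT and BMI may carry overlapping information.

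**4. Progression.** Expected events are 88 × 0.30 + 88 × 0.13 = 26.4 + 11.4, or about 38. Simulated results compare chi-square with logistic regression on treatment and the four factors (1,500 runs, Monte Carlo error about 0.6 points on type I error):

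| R² (approx.) | Type I error, chi-square vs logistic | Power, chi-square vs logistic |
|---|---|---|
| 0 | 5.9 vs 6.1 % | 79 vs 79 % |
| 0.05 | 5.1 vs 6.4 % | 81 vs 82 % |
| 0.16 | 3.5 vs 5.1 % | 80 vs 84 % |
| 0.28 | 2.3 vs 6.2 % | 83 vs 89 % |

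Power rises by 1 to 6 points where the factors are prognostic. The adjusted test sits at or somewhat above 5 %, so part of the apparent gain reflects a higher actual error rate.

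**5. Does the planned logistic model already do the job?** It contains treatment group, but its stated aim is to correlate progression with other variables, and it does not name the minimisation factors. It also includes EAT volume without saying at which time. If that is the 12-month value or the change, it is a post-randomisation primary outcome. The Background section proposes EAT reduction as the route to benefit, so conditioning on it would not estimate the total treatment effect.

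**The case against.** The strongest objections, and what stands of each:

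- **An adjusted model is planned.** A reader might infer that both primary outcomes are analysed only by unadjusted tests. The logistic regression contradicts that for progression. The objection stands that far, but for the reasons in step 5 the model does not serve as the adjusted treatment comparison.
- **The tests are not assigned to the primary outcomes.** The article calls them univariate and does not say which outcomes they serve. True, but it names no other two-group comparison, and for EAT there is no other candidate.
- **This is a condensed article.** The covariate list may sit in a full protocol or SAP, and the unnamed clinical variables may include the four factors. Missing detail alone would be no finding. The point rests on what the article does state: tests that do not match its own allocation method.
- **Baseline EAT is not ignored.** A reader might take it to be. The outcome is a change, so baseline enters by subtraction. Comparing ANCOVA with a test on the 12-month value alone would overstate the loss. Both change score and ANCOVA are valid in a randomised trial.
- **The factors may not matter.** BMI may predict the level of EAT more than its change. At R² = 0 the loss from omitting the factors is zero. This stands, and that case belongs in the range.

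**Conclusion.** The point holds as a loss of efficiency, and mainly for EAT. Against a change-score t test with 80 % power, baseline ANCOVA adds about 2 to 10 percentage points for correlations from 0.9 down to 0.5. Omitting the minimisation factors costs nothing at R² = 0. At R² of 0.1 to 0.3 it costs about 3 to 7 points of power, with the actual type I error falling to 3.8 to 1.9 %. The correlation, the R² and the biased-coin probability are assumptions; the documents fix none of them.

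For progression the benefit is smaller and not clearly established with about 38 events.

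A reader might infer from a miscalibrated test that false-positive findings become more likely or that the estimate is biased. Neither follows: the departure caused by omitting balanced factors is conservative, and the unadjusted comparisons remain valid.

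**What to change.** 1. **EAT, primary analysis:** ANCOVA of 12-month EAT volume (or of the change) on treatment, baseline EAT volume, age, sex, BMI and hypertension grade, reporting the adjusted difference with its 95 % CI.
2. **Progression:** estimate the treatment effect by logistic regression on treatment and the four minimisation factors, without post-randomisation EAT volume, and report a standardised risk difference with its 95 % CI. Keep the covariate set to these factors, given the expected number of events.
3. **Logistic model with EAT volume:** keep it as the analysis of the secondary outcome on the relationship between EAT and atherosclerosis, and say which EAT measurement enters.
4. **t and chi-square tests:** keep them as supportive, unadjusted results.

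The cost is analysis wording only, fixed before outcome data are examined. The four factors must be known at randomisation, and baseline EAT should come from the eligibility CCTA, so no extra data collection is expected.

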### Biomarkers

Two 10-ml samples of blood will be collected from the antecubital vein by a trained nurse for each individual. Fasting blood samples will be obtained between 7:00 a.m. and 12:00 noon to control for possible diurnal variations. Blood samples will be centrifuged at 4 °C and 3,000 rpm for 15 min. The serum will be sampled and stored at −80 °C until analysis. Traditional cardiovascular blood risk markers, including fasting blood glucose, triglycerides, total cholesterol, and high- and low-density lipoprotein cholesterol will be assessed. The following proinflammatory markers will be assessed: high-sensitivity C-reactive protein, IL-6, TNF-α, MCP-1, and MMP-9. In addition, NO and ET-1 will be measured, to assess endothelial function. Markers of adipose tissue inflammation and metabolism, including adiponectin and leptin, will also be assessed. These markers will be measured at baseline and 6 and 12 months after treatment.

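### The independent-samples t test named for the 14 serum markers makes no use of baseline and no provision for skewness; a baseline-adjusted analysis, on the log scale where needed, would recover power at almost no cost

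*Protocol article*

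**What the plan says.** The Statistical analysis section of the protocol article is one paragraph.

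- **Description:** continuous variables are summarised by mean and SD, or by "median and range in case of asymmetric distribution of data".
- **Testing:** the univariate tests are the chi-square test and t "tests for independent samples". No other between-group test for continuous data is named.
- **Model:** the only model is a logistic regression with coronary progression as its outcome, so it does not analyse the markers as outcomes.
- **Level:** "Statistical significance will be considered for" P < 0.05, with no distinction between outcomes.

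The Biomarkers section lists the markers in four groups: "fasting blood glucose, triglycerides, total cholesterol, and high- and low-density lipoprotein cholesterol will be assessed"; "high-sensitivity C-reactive protein, IL-6, TNF-α, MCP-1, and MMP-9"; "NO and ET-1 will be measured, to assess endothelial function"; and adipose markers "including adiponectin and leptin, will also be assessed". On timing it says: "These markers will be measured at baseline and 6 and 12 months after treatment". The Study outcomes section makes them secondary outcomes.

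**The concern.** The named test fits the data poorly in two ways.

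First, the paragraph expects that some variables will be asymmetric and changes the summary statistic for them, yet it keeps a comparison of means as the test. A marker could be reported as medians beside a P value for a difference in means, and a few large values could dominate that P value.

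Second, every patient supplies a baseline value and two follow-up values, while a two-sample t test takes one number per patient and has no place for a covariate. As written, the baseline value does not enter as an adjustment, and the text does not say how the 6- and 12-month values are combined or ranked.

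The mechanism aim rests on these markers, and the sample size was set on binary progression alone, so no power was planned for them. An inefficient test could miss real marker effects. Several unranked tests at 0.05 could also yield a chance finding that is then read as mechanism.

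**Working it through.** **1. The plan's own figure.** Inputs from Sample size calculation: progression 30 % versus 13 %, two-sided α = 0.05, β = 0.2, 1:1. With unpooled variance, n per arm = (1.960 + 0.842)² × (0.30×0.70 + 0.13×0.87) / 0.17² = 7.849 × 0.3231 / 0.0289 = 87.7, so 88 per arm and 176 in total. The stated 176 reproduces. It concerns binary progression only. It fixes the number available for the markers at 88 per arm, or 97 × 0.9 ≈ 87 after the expected losses.

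**2. Number of tests.** Markers: 5 (glucose, four lipids) + 5 (inflammatory) + 2 (endothelial) + 2 (adipose) = 14. With two post-baseline visits, 14 × 2 = 28 at most.
- 28 tests: expected false positives under the global null 28 × 0.05 = 1.4, whatever the correlation between tests. Chance of at least one, if independent: 1 − 0.95²⁸ = 76 %.
- One test per marker: 14 × 0.05 = 0.7, and 1 − 0.95¹⁴ = 51 % if independent.

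**3. Gain from baseline adjustment alone.** Assume a symmetric marker and an effect that gives the t test on follow-up values 80 % power at 88 per arm: δ = √(2/88) × (1.960 + 0.842) = 0.422 SD. ANCOVA multiplies the residual variance by 1 − ρ², so power = Φ(2.802/√(1 − ρ²) − 1.960).
- ρ = 0.3: Φ(0.977) = 83.6 %
- ρ = 0.5: Φ(1.275) = 89.9 %
- ρ = 0.7: Φ(1.963) = 97.5 %

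**4. Adding skewness.** These simulations assume log-normal markers. The log SD, effect and correlation are assumptions; the documents give none of them.

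Fixed effects, ρ = 0.6, 87 per arm, 4,000 trials per row, power in %:

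| Log SD | Ratio of geometric means | t, untransformed | t on untransformed change | t on log values | Log ANCOVA |
|---|---|---|---|---|---|
| 1.0 | 0.70 | 45.3 | 38.2 | 64.6 | 83.2 |
| 0.8 | 0.75 | 52.7 | 50.0 | 65.8 | 84.0 |
| 0.6 | 0.80 | 60.8 | 60.9 | 68.2 | 85.2 |

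The untransformed t test trails log ANCOVA by 37.9, 31.3 and 24.4 points. At log SD 0.6, the log scale accounts for 68.2 − 60.8 = 7.4 points and baseline adjustment for 85.2 − 68.2 = 17.0. At log SD 1.0 the two parts are 19.3 and 18.6.

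Effect set so that the log-scale t test has 80 % power, 88 per arm, 10,000 trials per setting:

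| Log SD | t, untransformed (ρ 0.5 / 0.7) | Log ANCOVA (ρ 0.5 / 0.7) | Loss in points |
|---|---|---|---|
| 0.5 | 74.9 / 75.0 | 89.5 / 97.4 | 14.6 / 22.4 |
| 0.8 | 67.4 / 66.6 | 89.1 / 97.5 | 21.7 / 30.9 |
| 1.0 | 59.8 / 60.8 | 89.3 / 97.6 | 29.5 / 36.8 |
| 1.2 | 53.8 / 53.3 | 89.6 / 97.4 | 35.8 / 44.1 |

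The ends of the range, simulated at 87 per arm with the same 0.422 SD effect (10,000 trials each):
- log SD 0.2, ρ = 0.3: 78.2 % versus 82.7 %, a loss of 4.5 points
- log SD 1.2, ρ = 0.6: 52.0 % versus 93.1 %, a loss of 41.1 points

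**5. Validity.** With no treatment effect, the untransformed t test rejected in 4.2 % to 4.9 % of trials across the settings of the second table. Skewness costs power here and does not inflate error.

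**The case against.** The strongest defence is that this is a condensed article and no analysis plan is shown. Transformations, covariates, repeated-measures models and multiplicity rules for secondary outcomes commonly sit in such a plan, and their absence here is not an error. That stands. What remains is that the article does make a choice: it names one test for continuous outcomes, and that test suits the collected data poorly.

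The second defence is that the text says less than a reader might infer. It does not say that the t test is on untransformed values, that follow-up values rather than changes are compared, or that each visit is tested separately. A t test on log values or on changes is also an independent-samples t test. So it would go too far to say that the plan runs 28 raw t tests; 28 is an upper count. Nor do the documents say that all 14 markers are skewed, and they give no distribution for any of them. This also stands. Changes on the untransformed scale would not help in the settings of the first table: power was lower than, or equal to, that for follow-up values.

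Third, the log-normal model with a multiplicative effect favours log ANCOVA by construction. That is fair, and it is why the result is given as a range.

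Finally, a reader might take the 76 % as the plan's false-positive risk. It assumes 28 independent tests, and correlation among markers and visits would lower it. The markers are secondary, and the mechanism aims are already worded as exploratory, so the missing multiplicity rule is minor.

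**Conclusion.** The point holds as a matter of efficiency. The only test named for continuous outcomes uses no baseline adjustment and makes no provision for the asymmetry that the same paragraph foresees.

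The loss against log-scale ANCOVA is about 5 points for a near-symmetric marker with correlation 0.3 and about 40 points for a strongly skewed one with correlation 0.6. It reaches 44 in the most extreme setting tried (log SD 1.2, correlation 0.7). These figures assume log-normal data, the stated effects and 87 or 88 patients per arm; where each marker falls in the range cannot be read from the documents.

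The documents do not support a claim that the marker tests are invalid, that much power is certainly lost on every marker, or that 28 tests are planned. If every marker were tested at both follow-up visits, 1.4 false positives would be expected under the global null. Labelling the results exploratory is a sufficient answer to that.

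**What to change.** In the Statistical analysis section, replace the t test for the markers with a baseline-adjusted analysis. Either of these will do:
- ANCOVA of the 12-month value on treatment and the baseline value; or
- a mixed model of the 6- and 12-month values with treatment, visit, treatment by visit and baseline, with the 12-month contrast as the one named test per marker.

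In both, adjust for the minimisation factors given under Randomization (age, sex, body mass index, hypertension grade). Log-transform the right-skewed markers, including their baseline values, and report geometric-mean ratios with 95 % CI. Label the marker results exploratory. Naming one contrast per marker cuts the upper count from 28 tests to 14 and the expected false positives from 1.4 to 0.7.

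This is a free improvement. The baseline samples are already part of the schedule, and nothing changes for patients or sample size. The only downsides are slightly more analysis and results stated as ratios, not raw differences, for the log-transformed markers.
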